**PART 3: FGD TOPIC GUIDES (3)**

**Domains, topic questions, and probes:** Use the table below to help you administer the questions during the interview.

| Domain     | Topic and Probes                                                                                                                                                                                               |
|-------------------|-----------------------------------------------------------------------------------------------------------------------------------------------------------------------------------------------------------------------|
|                   | 
b) What do these changes mean for you when you have a sick child?
 
c) What improvements would you like to see at your nearest health centre?
                                                             |
| 8. Closing | 
We are now approaching the end of our discussion. Is there anything else anyone would like to add about the kind of diagnosis and treatment you get from health centres or CMDs that we have not talked about?
 |

- ✓ **Summarize main points made by the participants;**
- ✓ **Thank participants**

# PART 4: NOTE-TAKER FORM

|                                                                                                                                                                                               |  |                                                                  |  |
|-----------------------------------------------------------------------------------------------------------------------------------------------------------------------------------------------|--|------------------------------------------------------------------|--|
| FGD ID number [ ] [ ] [ ]                                                                                                                                                                     |  | Moderator initials [ ] [ ] [ ]                                   |  |
| Sub-county code [ ]                                                                                                                                                                           |  | Note-taker initials [ ] [ ] [ ]                                  |  |
| FGD type
1 = Primary caregiver [ ] [ ]
2 = Heads of household [ ] [ ]                                                                                                                   |  | Gender of participants
1 = Male [ ] [ ]
2 = Female [ ] [ ] |  |
| Age of participants
1 = < 30 years [ ] [ ]
2 = ≥ 30 years [ ] [ ]                                                                                                                       |  | Health center in parish
1 = Yes [ ] [ ]
2 = No [ ] [ ]     |  |
| Date: [ ] [ ] / [ ] [ ] / [ ] [ ]

 day month year 
               |  | Time start [ ] [ ] : [ ] [ ]
Time end [ ] [ ] : [ ] [ ]       |  |
| 1. Meeting place description: detail and description, e.g. location, size and accessibility, and how this could affect the discussion; interruptions during the discussion                    |  |                                                                  |  |
| 2. Participant seating diagram:                                                                                                                                                               |  |                                                                  |  |
| 3. Group dynamics: general description – level of participation, dominant and passive participants, interest level, boredom, anxiety – and how these relate to the different topics discussed |  |                                                                  |  |
| 4. Impressions and observations:                                                                                                                                                              |  |                                                                  |  |
| 5. Notes of comments provided AFTER the discussion is over (Include additional sheets if necessary):                                                                                          |  |                                                                  |  |

| PART 5: CONTACT SUMMARY FORM (1)                                                                                                     |                                                                                                                           |
|--------------------------------------------------------------------------------------------------------------------------------------|---------------------------------------------------------------------------------------------------------------------------|
| FGD ID number [              ]                                                                                                | Moderator initials [              ]                                                                                |
| Sub-county code [    ]                                                                                                        | Note-taker initials [              ]                                                                               |
| FGD type
1 = Primary caregiver                      [         ]
2 = Heads of household                      [         ] | Gender of participants
1 = Male                      [         ]
2 = Female                      [         ] |
| Age of participants
1 = < 30 years                      [         ]
2 = ≥ 30 years                      [         ]     | Health center in parish
1 = Yes                      [         ]
2 = No                      [         ]     |
| Date:
[         ] / [         ] / [         ]
day                      month                      year                  | Time start [         ] : [         ]
Time end [         ] : [         ]                                  |
| 1. What were the main issues or points made by participants during this focus group?                                          |                                                                                                                           |

**PART 5: CONTACT SUMMARY FORM (2)**

**2. What new information did you gain through this focus group compared to previous focus groups in this study?**

**3. Was there anything surprising to you personally? Or that made you think differently about this research question?**

**4. What messages did you take from this interview for intervention design?**

**PART 5: CONTACT SUMMARY FORM (3)**

**5. How would you describe the general atmosphere and engagement of the focus group?**

**6. How would you describe the group dynamics? For example, were there dominant individuals (what was the result and what were their IDNOs)? Did all participants contribute? Did you feel there was pressure to adhere to dominant viewpoints (what topics)?**

**7. What else was important about this focus group?**

**8. Were there any problems with the topic guide (e.g. wording, order of topics, missing topics) you experienced in this focus group?**

## APPENDIX Z: STRUCTURED CONTEXTUAL RECORD

|                      |                                                                 |                                                        |                                                                     |
|----------------------|-----------------------------------------------------------------|--------------------------------------------------------|---------------------------------------------------------------------|
| Staff ID
[ ] [ ]  | Date completed
[ ] [ ] / [ ] [ ] / [ ] [ ]
day month year |                                                        |                                                                     |
| TIME PERIOD COVERED: | 1 = Baseline
2 = 0-3 months
3 = 4-6 months                | 4 = 7-9 months
5 = 10-12 months
6 = 13-15 months | 7 = 16-18 months
8 = 19-21 months
9 = 21-24 months
[ ] [ ] |

## SECTION 1: MALARIA CONTROL INTERVENTION COVERAGE

## INDOOR RESIDUAL SPRAYING (IRS)

| 1. Has IRS been conducted in the study area in the last 3 months?
If YES, go to Qn 2, otherwise skip to Qn 4 |                   | 1 = Yes 88 = Don't know
2 = No           |                  | [ ] [ ]                          |
|------------------------------------------------------------------------------------------------------------------------|-------------------|---------------------------------------------|------------------|----------------------------------|
| 2. What is the source of the information?                                                                              |                   | 1 = MoH 77 = Other
2 = USAID/PMI         |                  | [ ] [ ]                          |
| Location                                                                                                               | Dates of spraying | Formulation
1=ICON CS; 2=DDT
77=Other | Total population | Proportion of households sprayed |
| 3a.                                                                                                                    |                   | [ ] [ ]                                     |                  | [ ] [ ] %                        |
| 3b.                                                                                                                    |                   | [ ] [ ]                                     |                  | [ ] [ ] %                        |
| 3c.                                                                                                                    |                   | [ ] [ ]                                     |                  | [ ] [ ] %                        |
| 3d.                                                                                                                    |                   | [ ] [ ]                                     |                  | [ ] [ ] %                        |
| 3e.                                                                                                                    |                   | [ ] [ ]                                     |                  | [ ] [ ] %                        |

## INSECTICIDE-TREATED BEDNETS (ITNs)

| Indicator                                                                    | Numerators (N) & Denominators (D)                      | Proportion or mean |
|------------------------------------------------------------------------------|--------------------------------------------------------|--------------------|
| 4. Proportion of households with at least one bednet                         | N=[ ] [ ] [ ] [ ] [ ] [ ]
D=[ ] [ ] [ ] [ ] [ ] [ ] | [ ] [ ] %          |
| 5. Proportion of households with at least one ITN                            | N=[ ] [ ] [ ] [ ] [ ] [ ]
D=[ ] [ ] [ ] [ ] [ ] [ ] | [ ] [ ] %          |
| 6. Mean number of nets per household                                         | D=[ ] [ ] [ ] [ ] [ ] [ ]                              | [ ] [ ] • [ ]      |
| 7. Mean number of ITNs per household                                         | D=[ ] [ ] [ ] [ ] [ ] [ ]                              | [ ] [ ] • [ ]      |
| 8. Proportion of children under five who slept under any net the prior night | N=[ ] [ ] [ ] [ ] [ ] [ ]
D=[ ] [ ] [ ] [ ] [ ] [ ] | [ ] [ ] %          |
| 9. Proportion of children under five who slept under an ITN the prior night  | N=[ ] [ ] [ ] [ ] [ ] [ ]
D=[ ] [ ] [ ] [ ] [ ] [ ] | [ ] [ ] %          |

## ARTEMISININ-BASED COMBINATION THERAPY

| Indicator                                                          | Numerators (N) & Denominators (D)                      | Proportion |
|--------------------------------------------------------------------|--------------------------------------------------------|------------|
| 10. Proportion of febrile episodes in children treated with an ACT | N=[ ] [ ] [ ] [ ] [ ] [ ]
D=[ ] [ ] [ ] [ ] [ ] [ ] | [ ] [ ] %  |
| 11. Proportion of malaria cases treated with an ACT                | N=[ ] [ ] [ ] [ ] [ ] [ ]
D=[ ] [ ] [ ] [ ] [ ] [ ] | [ ] [ ] %  |

## STRUCTURED CONTEXTUAL RECORD (2)

|                     |                                                                 |
|---------------------|-----------------------------------------------------------------|
| Staff ID
[ ] [ ] | Date completed
[ ] [ ] / [ ] [ ] / [ ] [ ]
day month year |
|---------------------|-----------------------------------------------------------------|

## SECTION 2: HEALTH FACILITY LEVEL

|                        |              |                    |                 |                      |
|------------------------|--------------|--------------------|-----------------|----------------------|
| Health facility codes: | 1 = Maundo   | 6 = Nawire         | 11 = Petta      | 16 = Mwelo           |
|                        | 2 = Were     | 7 = Kirewa         | 12 = Makawari   | 17 = Lwala           |
|                        | 3 = Katajula | 8 = Chawolo Kirewa | 13 = Mbula      | 18 = Panyangasi      |
|                        | 4 = Paya     | 9 = Kisoko         | 14 = Gwaragwara | 19 = Mudodo          |
|                        | 5 = Pusere   | 10 = Morkiswa      | 15 = Osia       | 20 = Chawolo Mulanda |

## STAFFING

1. Have there been any changes to health center STAFF in the last 3 months? 1 = Yes 88 = Don't know  
2 = No [ ] [ ]

*If YES, go to Qn 2, otherwise skip to Qn 3.*

| Health center code | HW position                                                                 | Change                                        | Source of information                                   |
|--------------------|-----------------------------------------------------------------------------|-----------------------------------------------|---------------------------------------------------------|
|                    | 1=In-charge; 2 = Nursing aide/asst;
3 = Volunteer; 77 = Other (describe) | 1=Joined HC; 2 = Left HC
3 = On leave/away | 1 = HC in-charge; 2 = District;
3 = MoH ; 77 = Other |
| 2a. [ ] [ ]        | [ ] [ ]                                                                     | [ ]                                           | [ ] [ ]                                                 |
| 2b. [ ] [ ]        | [ ] [ ]                                                                     | [ ]                                           | [ ] [ ]                                                 |
| 2c. [ ] [ ]        | [ ] [ ]                                                                     | [ ]                                           | [ ] [ ]                                                 |
| 2d. [ ] [ ]        | [ ] [ ]                                                                     | [ ]                                           | [ ] [ ]                                                 |
| 2e. [ ] [ ]        | [ ] [ ]                                                                     | [ ]                                           | [ ] [ ]                                                 |

## INTERVENTIONS

3. Have any new INTERVENTIONS been introduced at the health centers in the last 3 months? 1 = Yes 88 = Don't know  
2 = No [ ] [ ]

*If YES, go to Qn 4, otherwise skip to Qn 5.*

| Health center code | Name of program/donor | Intervention | Source of information                                   |
|--------------------|-----------------------|--------------|---------------------------------------------------------|
|                    |                       |              | 1 = HC in-charge; 2 = District;
3 = MoH ; 77 = Other |
| 4a. [ ] [ ]        |                       |              | [ ] [ ]                                                 |
| 4b. [ ] [ ]        |                       |              | [ ] [ ]                                                 |
| 4c. [ ] [ ]        |                       |              | [ ] [ ]                                                 |
| 4d. [ ] [ ]        |                       |              | [ ] [ ]                                                 |
| 4e. [ ] [ ]        |                       |              | [ ] [ ]                                                 |

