### 3.2. SECONDARY OBJECTIVES

1. To develop a comprehensive logic model of the ACT PRIME HFI with intervention components mapped through to their intended effects and outcomes.
2. To evaluate the process of the HFI implementation including health worker training, health center management tools, supply of AL and RDTs for malaria, and interactions with local and district stakeholders.
3. To develop a rich contextual record of factors that may have affected the HFI implementation outcomes such as other interventions or programmes implemented in the area, changes to malaria case management guidelines, and other environmental, economic, political or individual factors.
4. To assess the wider expected and unexpected impacts of the HFI at the household, community, private sector, and public health system levels.

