#### **4.4.1. Structured contextual record**

The structured contextual record will involve the recording of details about factors that may affect ACT PRIME implementation and impact at three-monthly intervals by the implementing team. A structured record format will be used to document these contextual factors for each health center, and at the district level.

Factors may include the following:

- Other interventions involving malaria at the community level in the trial area
- Other research involving malaria at the community level in the trial area
- Other interventions at the health center level in the trial area
- Other research at the health center level in the trial area
- Other training programmes involving CMDs or health center staff involved in the trial
- Specific personalities or political problems at any communities/health center
- Change of staff at health center
- Change of community medicine distributor or village health team members
- Guideline changes about malaria testing and treatment at health centers/elsewhere
- Messages or news stories about malaria testing on radio/TV/newspapers
- Level of support (low, medium, high) from district health management team for the intervention
- Other local or national economic or political factors that may have impacted the delivery or receipt of this intervention

The source of each item added to the local context document will be noted on the document. The data collected in these tables will be assimilated into a report of concurrent activities and other contextual factors overall. Factors that varied widely will be used in the final analysis of the intervention impact as potential explanatory variables.

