## TRAINING PROGRAMS

5. Have any new TRAINING PROGRAMS been introduced at the health centers in the last 3 months? 1 = Yes 88 = Don't know  
2 = No [ ] [ ]

*If YES, go to Qn 6, otherwise skip to Qn 7.*

| Health center code | HWs participating | Description of training | Source of information                                   |
|--------------------|-------------------|-------------------------|---------------------------------------------------------|
|                    |                   |                         | 1 = HC in-charge; 2 = District;
3 = MoH ; 77 = Other |
| 6a. [ ] [ ]        |                   |                         | [ ] [ ]                                                 |
| 6b. [ ] [ ]        |                   |                         | [ ] [ ]                                                 |
| 6c. [ ] [ ]        |                   |                         | [ ] [ ]                                                 |

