## RESEARCH PROGRAMS INVOLVING HEALTH CENTERS OR STAFF

7. Have any new RESEARCH PROGRAMS been introduced at the health centers in the last 3 months? 1 = Yes 88 = Don't know  
2 = No [ ] [ ]

*If YES, go to Qn 8, otherwise skip to next section.*

| Health center code | Name of research group | Project details | Source of information                                   |
|--------------------|------------------------|-----------------|---------------------------------------------------------|
|                    |                        |                 | 1 = HC in-charge; 2 = District;
3 = MoH ; 77 = Other |
| 8a. [ ] [ ]        |                        |                 | [ ] [ ]                                                 |
| 8b. [ ] [ ]        |                        |                 | [ ] [ ]                                                 |
| 8c. [ ] [ ]        |                        |                 | [ ] [ ]                                                 |

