**STRUCTURED CONTEXTUAL RECORD (4)**

Staff ID

[ ][ ]

Date completed

[ ][ ] / [ ][ ] / [ ][ ]  
day month year**SECTION 3: COMMUNITY LEVEL****MALARIA-RELATED HEALTH PROGRAMS****9. Have any new health programs related to MALARIA been introduced in the community in the last 3 months?**

1 = Yes 88 = Don't know

2 = No

[ ][ ]

*If YES, go to Qn 10, otherwise skip to Qn 11.*

| Sub-county code | Area involved                        | Summary of program | Source of information                                |
|-----------------|--------------------------------------|--------------------|------------------------------------------------------|
|                 | List parishes, or villages, if known |                    | 1 = HC in-charge; 2 = District; 3 = MoH ; 77 = Other |
| 10a. [ ][ ]     |                                      |                    | [ ][ ]                                               |
| 10b. [ ][ ]     |                                      |                    | [ ][ ]                                               |
| 10c. [ ][ ]     |                                      |                    | [ ][ ]                                               |
| 10d. [ ][ ]     |                                      |                    | [ ][ ]                                               |
| 10e. [ ][ ]     |                                      |                    | [ ][ ]                                               |

**NON-MALARIA HEALTH PROGRAMS****11. Have any new health programs that are not related to malaria been introduced in the community in the last 3 months?**

1 = Yes 88 = Don't know

2 = No

[ ][ ]

*If YES, go to Qn 12, otherwise skip to Qn 13.*

| Sub-county code | Area involved                        | Summary of program | Source of information                                |
|-----------------|--------------------------------------|--------------------|------------------------------------------------------|
|                 | List parishes, or villages, if known |                    | 1 = HC in-charge; 2 = District; 3 = MoH ; 77 = Other |
| 12a. [ ][ ]     |                                      |                    | [ ][ ]                                               |
| 12b. [ ][ ]     |                                      |                    | [ ][ ]                                               |

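### The structured contextual record asks only about newly introduced programmes, even at baseline, so it gives no inventory by health centre of programmes already running or later withdrawn

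*Supplement*

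**What the plan says.** Secondary objective 3 (section 3.2) is to build a rich contextual record of factors that may have affected the health facility intervention (HFI), "such as other interventions or programmes implemented in the area".

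Section 4.4.1 lists what the structured part may cover, for example "Other interventions at the health center level in the trial area", with parallel entries for research and training. None is limited to new activity. On the level of recording: "A structured record format will be used to document these contextual factors for each health center, and at the district level". On use: "Factors that varied widely will be used in the final analysis of the intervention impact as potential explanatory variables".

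Appendix Z is the form. It is completed every three months, and its list of time periods starts with a baseline code. Its programme questions include:

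- "Have any new INTERVENTIONS been introduced at the health centers in the last 3 months" (Qn 3)
- "Have any new TRAINING PROGRAMS been introduced at the health centers in the last 3 months" (Qn 5)
- "Have any new RESEARCH PROGRAMS been introduced at the health centers in the last 3 months" (Qn 7)
- "Have any new health programs related to MALARIA been introduced in the community in the last 3 months" (Qn 9)

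Qns 11 (non-malaria programmes), 13 (community health worker training) and 15 (community research) are worded the same way.

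**The concern.** The form is narrower than the section it implements. Section 4.4.1 wants to know what else was operating at each centre; Appendix Z records only what arrived in the preceding three months. For a programme already established when recording begins, the right answer is No at baseline and No at each later period. For one that starts during the study, the start is entered once, but nothing on the programme items shows whether it is still running or has been withdrawn.

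The record is meant to help explain why the HFI worked or did not, and its entries are candidates for explanatory variables across 20 centres, 10 per arm. If existing support is not recorded, supported and unsupported centres receive the same value. The analyst then cannot tell whether the factor varied widely, which is the plan's own condition for using it. Withdrawal of outside support during the study could likewise be mistaken for a success or failure of the HFI.

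**Working it through.** The plan gives no figure to reproduce. The check compares the form with the section it serves, then with the other tools.

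**1. Programme questions.** In Appendix Z these are Qns 3, 5 and 7 (health facility) and 9, 11, 13 and 15 (community). Limited to new items in the last 3 months: 7 of 7. The policy question (Qn 19) has the same limit but is not counted here.

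**2. Baseline.** Period code 1 is Baseline. No separate baseline question or list of existing programmes is printed.

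**3. A programme present throughout.** The synopsis gives about 1½ years. Three-monthly records over 18 months give 18 ÷ 3 = 6 periods, plus baseline = 7 records. The form itself carries 9 period codes. A programme that began before the baseline look-back and never stopped is entered in 0 of 7 records, or 0 of 9 if every code is used.

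**4. How far back baseline reaches.** The documents do not say when the baseline form is completed, so any cut-off is an assumption:

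| Assumed completion | Look-back of 3 months reaches |
|---|---|
| December 2010 (ACT PRIME start, section 1.2) | about September 2010 |
| March 2011 (roll-out, section 1.2) | about December 2010 |

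The point does not depend on which applies.

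**5. Stopping.** The answer rows under the seven questions have no field for an end or withdrawal. The staffing rows on the same form do code joining, leaving and absence, so start/stop recording is already within the form's design.

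**6. Do other tools supply the missing inventory?**

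| Source | What it adds | Limit |
|---|---|---|
| Implementer interviews (Appendix Q, up to 5) | Any other malaria or health programme | About 9-12 months after roll-out; asks about the area, with a community or health-centre probe |
| Stakeholder interviews (Appendix S, up to 10) | Other programmes and current training | About one year after roll-out; the probe for which centres is attached to staffing, re-stocking, information and relationships, not to other programmes |
| Health worker interviews (Appendix R, up to 10) | Other training, materials or tools; carries a centre code | HFI arm only |
| Community health worker focus groups (8, both arms) | Current activities, recent training, drug supply | Each pools the catchments of 5 health centres (section 5.8.2) |
| Trainee background forms (Appendices D and H) | Workshops in the past 3 years | HFI arm only |
| Net and ACT coverage (Appendix Z, Section 1) | Current levels, whatever the start date | No health-centre column; does not identify programmes |
| Health worker semi-structured questionnaire (Appendix U) | Aims to reach every facility in both arms | No question on other programmes |

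No row gives programme presence by health centre, in both arms, over time.

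**The case against.** The strongest reply is that Appendix Z is one source among several. Section 4.4 assigns the context evaluation to interviews and focus groups as well, and several guides ask about other programmes without restricting them to new ones. Much malaria-control exposure is captured as current net and ACT coverage. Withdrawal is not wholly invisible: staff departures are recorded by centre, stakeholders are asked about changes in staffing and re-stocking, and drug and RDT supply is tracked at HFI centres. Randomisation balances stable pre-existing programmes in expectation. The promised standard operating procedures and the earlier district survey, neither of which is shown, might also supply a baseline picture.

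Much of this stands. A reader might infer from the form that existing programmes are never recorded at all, or that objective 3 cannot be met. The documents support neither reading, because the other tools do capture some continuing activity. The argument about imbalance between arms is also only a possibility: the documents give no figure for how many centres have outside support.

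What the reply does not remove is the mismatch with section 4.4.1. That section promises documentation by health centre in a structured form, and the other sources cannot rebuild it. Balance in expectation does not guarantee balance with 10 centres per arm, and it does not help explain why the HFI worked in some centres and not in others. Procedures that are not shown cannot be relied on to override the printed questions.

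**Conclusion.** The point holds in a limited form. Completed as printed, the structured record gives no inventory, by health centre and in both arms, of programmes already running at baseline or withdrawn later. All 7 programme questions are affected, at all 20 centres and at every record. This is narrower than section 4.4.1 and weakens the planned use of these factors as explanatory variables. Objective 3 is partly served through the other tools.

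The conclusion rests on two assumptions: that the form is completed literally, and that no unseen procedure adds a baseline list. How much information is lost depends on how many centres have existing support, which the documents do not say. The change is worth making because it is cheap, and because a missed baseline can be rebuilt later only from recall.

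**What to change.** For period 1 (Baseline), reword Qns 3, 5, 7, 9, 11, 13 and 15 to list the programmes currently active, by health centre code (facility items) or sub-county code (community items), with the start date of each. For later periods, ask which programmes have started or stopped since the last record, and add a start/stop code modelled on the one already used for staffing. Each centre's programme exposure can then be followed over time in both arms.

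If a fixed earliest date is wanted for interpretation, state when the baseline form is completed.

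The cost is rewording one form that the study team fills in, one extra code and a slightly longer baseline record. No extra visits or participants are needed.
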